Several risk factors for shoulder and upper body problems after breast cancer treatment have been identified, including treatment-related factors, such as type of axillary surgery and RT, and patient factors such as age, body mass index (BMI) and pre-existing shoulder problems.^4 5^ Women undergoing mastectomy compared with breast conserving surgery are at greater risk of postoperative shoulder restrictions (OR 5.7, 95% CI 1.03 to 31.2).^4^ Additionally, those undergoing axillary lymph node clearance (ANC) are at greater risk of postoperative arm complaints compared with those having sentinel lymph node biopsy (OR 9.8; 95% CI 3.5 to 27.5).^4–6^ RT, particularly to the axilla or chest wall, increases the odds of shoulder restriction (pooled OR 1.7, 95% CI 1.0 to 2.9) and lymphoedema (pooled OR 1.5, 95% CI 1.2 to 1.8) compared with women treated without adjuvant RT.^4^ Women reporting problems in the upper body and shoulder region before surgery are also at increased risk of chronic postoperative pain.^5 7^ BMI at time of surgery has been shown to have an independent negative effect on shoulder external rotation up to 7 years after breast cancer treatment, and increased BMI is a risk factor for chronic postoperative pain and arm lymphoedema.^7 8^ It is important that the UK National Health Service (NHS) provides optimal care for these women at high risk of developing shoulder problems to ensure recovery and return to usual activities after cancer treatment.

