### Eligibility criteria

Women are eligible to participate in PROSPER if they are: diagnosed with histologically confirmed invasive or non-invasive primary breast cancer scheduled for surgical excision; aged 18 years or over; can comply with the protocol; willing to provide written informed consent and considered as being at high risk of developing postoperative shoulder problems (table 2). This is a pragmatic trial and it is important that inclusion criteria reflect contemporary clinical practice. Therefore, women are also eligible where a later decision is made for postoperative RT to the axilla and/or supraclavicular region, thus changing their risk status from low to high. ‘Late entry’ women are eligible for the trial if the decision for postoperative RT is made within 6 weeks of surgery. Women who have had previous breast surgery (such as excision of a benign tumour or breast cyst) and those women who have had previous contralateral (opposite side) mastectomy, are eligible for invitation providing they fulfil high-risk criteria for shoulder problems. Women having immediate reconstruction or bilateral breast surgery are ineligible as the usual NHS postoperative care pathway often includes routine postoperative physiotherapy. Exclusion criteria are presented in table 2.

**Table 2 T2:** Trial inclusion and exclusion criteria

Inclusion criteria	Exclusion criteria
Age ≥18 years	Males
Histologically confirmed invasive or non-invasive primary breast cancer scheduled for surgical excision of breast cancer	Women having immediate reconstructive surgery
Considered high risk of developing shoulder problems after surgery defined by one or more of the following: Planned axillary node clearance Planned radiotherapy to the axilla and/or supraclavicular* Existing shoulder problems (based on PROSPER screening criteria)	Women having SLNB, with or without breast surgery, unless they fulfil other high-risk criteria
Obesity defined as body mass index >30	Women having bilateral breast surgery
Any subsequent axillary surgery related to primary surgery, eg, axillary lymph node clearance conducted after SLNB	Evidence of metastatic disease at time of recruitment
Able to provide written informed consent	
Willing and able to comply with the protocol	

*Includes women informed of need for radiotherapy to the axilla and/or supraclavicular within 6 weeks of surgery, thus potential late entry to the trial is allowed in this setting.

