### Allocation sequence generation and randomisation

Randomisation is based on a computer-generated algorithm held and controlled centrally by the Warwick Clinical Trials Unit (WCTU) programming team, independent from the PROSPER team. The WCTU telephone randomisation service is used whereby randomisation occurs after eligibility and informed consent has been obtained. Concealment of allocation is maintained. An automated confirmation email of intervention allocation is generated to the study team. Randomisation is stratified by the following variables: (i) first versus repeat surgery; (ii) centre and (iii) whether informed of the need for RT within 6 weeks of surgery. The first variable adjusts for the requirement for any additional surgery which may change risk status from low to high (eg, second procedure ANC or re-excision of surgical margins). The second stratification variable ensures balanced allocation across each recruitment site. The third variable accounts for late entry to the trial, thus relates to the timing of intervention delivery and whether participants are randomised preoperatively (up to the day of surgery) or within the first 6 weeks postoperatively. Due to the nature of the study intervention, it is not possible to blind participants or treating physiotherapists to treatment allocation. However, receipt and handling of outcome data collection is blinded, thus data entry of returned postal questionnaires, data cleaning and interim statistical analyses are conducted without knowledge of treatment allocation (blinded).

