### Data analysis

Statistical analysis will be intention-to-treat and will comply with the Consolidated Standards of Reporting Trials (CONSORT) guidelines. The primary outcome data will be summarised using mean, SD, median and range values. The clustering effect will be assessed prior to analysis of the data. In the presence of a clustering effect, the primary outcome will be analysed using multilevel linear regression models. If there is negligible clustering effect, it will be analysed using ordinary linear regression models. In each case, the mean change from baseline (to 6 and 12 months) will be summarised for each of the treatment arms and differences between the interventions using unadjusted and adjusted (for age, type of surgery and RT) estimates. These mean changes and their 95% CIs will be plotted graphically so that change can be assessed over the course of the study. Continuous secondary outcomes will be assessed in a similar way to the primary outcome. Categorical data will be analysed using random effect/ordinary logistic models, depending on the presence of a clustering effect.

A DASH score cannot be computed if there are more than three missing items. As a sensitivity analysis, the impact of missing data will be assessed using multiple imputation. The impact of non-compliance with the intervention will be examined using the complier average causal effect (CACE) analysis.^20 21^ We have reviewed definitions of compliance for CACE analyses used in other therapy trials.^22 23^ Complete compliance with the PROSPER intervention is defined as having three or more contacts with the PROSPER therapist; an additional analysis will be undertaken to explore partial compliance, defined as less than three sessions. Analyses and template tables will be reported in a detailed statistical analysis plan for review and approval by the Data Monitoring Committee (DMC), prior to final statistical analysis of the data. Planned sensitivity analyses include: a) the impact of low/high recruitment centres on clustering effect and b) assessment of differences between date of randomisation and date of surgery across groups, as surgical trials vary in relation to timing of follow-up.

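### The stated adjusted model omits BMI and existing shoulder problems, which the protocol treats as risk factors, so a little precision on DASH and continuous pain outcomes may be forgone

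*Protocol article*

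**What the plan says.** The Data analysis section fixes three adjustment variables for the primary outcome: "differences between the interventions using unadjusted and adjusted (for age, type of surgery and RT) estimates". The outcome takes the form of a change score: "the mean change from baseline (to 6 and 12 months) will be summarised for each of the treatment arms". Continuous secondary outcomes are to be handled in much the same way, and categorical ones by logistic models.

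The Background lists treatment factors (axillary surgery, RT) and "patient factors such as age, body mass index (BMI) and pre-existing shoulder problems" as risk factors for shoulder and upper body problems. It adds that "BMI at time of surgery has been shown to have an independent negative effect on shoulder external rotation", links higher BMI to chronic pain and lymphoedema, and states: "Women reporting problems in the upper body and shoulder region before surgery are also at increased risk of chronic postoperative pain".

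Table 2 (Eligibility criteria) includes "Existing shoulder problems (based on PROSPER screening criteria" and "Obesity defined as body mass index >30". The obesity entry sits on its own row and is read here as one of the high-risk routes.

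Randomisation is stratified by "i) first versus repeat surgery; (ii) centre and (iii) whether informed of the need for RT within 6 weeks of surgery". Neither BMI nor shoulder status is a stratifier.

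**The concern.** The article does not leave the covariates open; it names them. The named set broadly covers three of the five risk factors in the Background (surgery, RT, age) and omits the other two without giving a reason. Yet the trial regards each of those two as prognostic enough to qualify a woman as high risk. Because women enter by different routes, the sample will be mixed on both factors. Randomisation follows confirmation of eligibility, so values taken at screening cannot be affected by allocation and are valid covariates.

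In a linear model, leaving out a baseline variable that predicts the outcome leaves its variance in the residual. The treatment estimate is then somewhat less precise than it could be, and a chance imbalance on that variable is not adjusted for. This applies to DASH and to pain scores analysed as continuous. The case from the Background is more direct for pain, because pain is an outcome it ties to both factors.

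**Working it through.** **1. Reproduce the plan's figures.** Inputs from the Sample size section: difference 7 DASH points, 80% power, P<0.05 (two-sided assumed), 242 women in total, design effect 1.05, 25% loss, target 350.

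- 242 × 1.05 = 254.1 (stated: 256).
- 256 / 0.75 = 341.3, rounded up to 342 (stated: 350).

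Both agree to within 3%. No SD is stated, so 242 cannot be checked on its own. Solving the two-sided normal formula for the SD:

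SD = 7 × √(121/2) / (1.960 + 0.842) = 7 × 7.778 / 2.802 ≈ 19.4, a standardised difference of about 0.36.

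The article does not say whether this SD belongs to the 12-month score or to the change score.

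**2. Effect of extra covariates.** If the two factors explain a further share R² of the variance of the analysed outcome, the residual SD is 19.43 × √(1 − R²). The article gives no R², so every value here is an assumption. With 121 women analysed per arm, power = Φ(7 / (SD_res × √(2/121)) − 1.960) and the 95% CI half-width = 1.96 × SD_res × √(4/242).

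| Assumed extra R² | Power | CI half-width (points) |
|---|---|---|
| 0 | 80.0% | 4.90 |
| 0.01 | 80.4% | 4.87 |
| 0.02 | 80.8% | 4.85 |
| 0.05 | 82.0% | 4.77 |
| 0.10 | 84.0% | 4.65 |
| 0.15 | 86.0% | 4.52 |

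Worked case, R² = 0.05: 19.43 × √0.95 = 18.94; 7 / (18.94 × 0.1286) = 2.874; 2.874 − 1.960 = 0.914; Φ(0.914) = 82.0%.

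**3. Which R² is plausible?** A binary factor with prevalence p that shifts the analysed outcome by b points explains p(1 − p)b² / SD². With p from 0.2 to 0.5, b = 5 gives about 1% to 2% and b = 10 gives about 4% to 7%. For example, 0.2 × 0.8 × 25 / 377.7 = 0.011.

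The change score already removes part of any existing shoulder problem. In a simulation with illustrative inputs (20% of women with a shoulder problem, baseline DASH 5 to 15 points higher in them, correlation of 12-month with baseline score 0.4 to 0.6, further 12-month shift 0 to 5 points), the shoulder flag explained about 0% to 3% of change-score variance. With baseline DASH as a covariate it explained about 0% to 1.5%. A range of 1% to 5% for both factors together is therefore reasonable, and 10% is optimistic.

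**4. Comparison with the baseline score as a covariate.** With equal variances and correlation ρ, the residual variance relative to a change score is (1 − ρ²) / (2(1 − ρ)) = (1 + ρ)/2. For assumed ρ of 0.4 to 0.7 this is 0.70 to 0.85, a cut of 15% to 30%. That is larger than BMI and shoulder status are likely to add.

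**The case against.** The strongest reply is that nothing here is an error. The protocol never undertakes to adjust for every risk factor it names. Omitting a prognostic covariate does not bias a randomised comparison, and the sample size claims no gain from covariates. All of that stands. It is also said that covariates belong in the statistical analysis plan, which is not shown and may extend the list. That stands only in part, because the article states a specific list, which a plan written to follow it would carry over.

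Four stronger readings are tempting, and the article does not support them.

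- A reader might infer that precision on the primary outcome is definitely lost. The Background ties BMI to shoulder rotation, pain and lymphoedema, and earlier shoulder problems to chronic pain. It gives no association of either with DASH or its change, so the gain could be close to zero.
- A reader might infer that chance imbalance on these factors is dealt with nowhere. Change from baseline absorbs part of any existing shoulder problem. This reply is weaker for BMI, which is not a component of DASH.
- A reader might expect the same gain for every secondary outcome. In a logistic model, adding a prognostic covariate generally widens the interval for the treatment log-odds ratio and changes the estimand from marginal to conditional. Power may still rise.
- A reader might assume that the data are already complete. One high-risk criterion is enough to enter, so a woman admitted for planned node clearance need not have been assessed on the others. Table 3 lists neither BMI nor a shoulder-screening flag, and Table 2 gives BMI only as a threshold. The baseline forms are not shown.

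**Conclusion.** The point holds as a modest recommendation. The stated adjustment set leaves out two pre-randomisation factors that the protocol itself treats as prognostic, so some precision on DASH and continuous pain outcomes may be forgone. The likely size is about 0.4 to 2 percentage points of power, or 0.03 to 0.13 DASH points off the CI half-width (4.90 to 4.87 and 4.77).

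This rests on an SD back-solved from 242 women, a two-sided 5% test, and an assumed extra R² of 1% to 5%. The planned 80% power and the validity of the comparison are unaffected. The section reports both an unadjusted and an adjusted estimate without saying which is primary; if it is the unadjusted one, longer adjustment would not change the primary inference.

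**What to change.** Where they are recorded at screening or baseline for all women, add BMI (continuous, or the over-30 flag if only that is available) and existing shoulder problem (yes/no) to the prespecified adjusted model for DASH and continuous pain scores. Enter the baseline score as a covariate in the same edit, since it probably brings the larger gain. If the same covariates are used in the logistic models, give the reason as possible power and control of chance imbalance, and report the odds ratio as conditional. State which estimate, adjusted or unadjusted, is primary.

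The cost is a line or two of text, about two degrees of freedom for BMI and shoulder status out of some 240 to 260 women analysed, and a stated rule for missing covariate values. The change should be made before allocation is unblinded, because covariates added afterwards are open to challenge. If either variable turns out not to have been collected for everyone, check its completeness before committing to it.

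### The stated adjustment set does not name the randomisation stratifiers, and centre is kept only if a clustering check finds an effect: a small, conservative mismatch

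*Protocol article*

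**What the plan says.** The section on allocation sequence generation and randomisation states: "Randomisation is stratified by the following variables: (i) first versus repeat surgery; (ii) centre and (iii) whether informed of the need for RT", with a 6-week window after surgery for the third. It also explains two of these factors. Of first versus repeat surgery it says: "The first variable adjusts for the requirement for any additional surgery which may change risk status from low to high". Of the RT factor it says: "The third variable accounts for late entry to the trial, thus relates to the timing of intervention delivery".

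The Data analysis section lists the covariates: "unadjusted and adjusted (for age, type of surgery and RT) estimates". It makes the form of the model depend on the data. On one branch, "In the presence of a clustering effect, the primary outcome will be analysed using multilevel linear regression models". On the other, "If there is negligible clustering effect, it will be analysed using ordinary linear regression models". One planned sensitivity analysis concerns "the impact of low/high recruitment centres on clustering effect", which links clustering to centre. The Sample size section, by contrast, speaks of therapist effects. A detailed statistical analysis plan is announced but is not shown.

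**The concern.** When randomisation forces balance on factors that predict the outcome, the treatment estimate varies less than it would under simple randomisation. A model without those factors does not take credit for this. It leaves their variance in the residual, so the standard error is too large, the test rejects less often than its nominal level, and some power is lost.

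The article gives reason to think the stratifiers might be prognostic. Repeat surgery is said to be able to change a woman's risk status. Late entrants are recruited after surgery and the others before it, so baseline questionnaires completed at recruitment describe different clinical states, and the plan summarises change from baseline. At stake is a little precision in the primary comparison, together with the principle that the analysis should follow the design.

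**Working it through.** **Stratifiers against covariates**

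| Stratifier | Nearest item in the analysis | Same thing? |
|---|---|---|
| First versus repeat surgery | Type of surgery | Not defined as such. The stratifier records the need for a further procedure, not which operation was done. |
| Late entry after an RT decision | RT | Not defined as such. Planned RT is also an entry route before surgery (Eligibility criteria, Table 2), so an RT term can combine early and late entrants. |
| Centre | Possible random effect | Only if clustering is found and centre is the clustering unit. Otherwise ordinary regression is used and centre drops out. |

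**The plan's own figure.** Inputs from the Sample size section are a difference of 7 DASH points, 80% power, P<0.05 (taken as two-sided) and 242 participants. No SD is stated, so it is solved for:

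- n per arm = 2 × SD² × (1.960 + 0.842)² / 7². An SD of 19.4 gives 120.6, so 121 per arm and 242 in total, as stated. Solving exactly for 121 per arm gives SD 19.43.
- 242 × 1.05 = 254.1, against 256 stated. 256 / 0.75 = 341.3, against 350 stated. Both are close, and nothing below depends on them.
- The standard error at 121 per arm is 19.43 × √(2/121) = 2.50.

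**Effect of omitting balanced stratifiers.** Let R² be the share of outcome variance that the stratifiers explain beyond age, type of surgery, RT and any centre effect in the model. The documents give no value, so 1% to 10% is an assumed range. The implied SD is treated as what remains after the listed covariates, and balance is treated as complete.

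- Reported SE / true SE = 1/√(1 − R²)
- True type I error = 2 × [1 − Φ(1.96/√(1 − R²))]
- Power with stratifiers omitted = Φ[(7 − 1.96 × 2.50) / (2.50 × √(1 − R²))]
- Power with stratifiers included = Φ[7 / (2.50 × √(1 − R²)) − 1.96]

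For R² = 5%, 1/√0.95 = 1.026. The critical value becomes 1.96 × 1.026 = 2.011, and the two-sided tail is 4.4%.

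| Residual R² (assumed) | SE too large by | True type I error | Power, omitted | Power, included |
|---|---|---|---|---|
| 1% | 0.5% | 4.9% | 80.1% | 80.4% |
| 5% | 2.6% | 4.4% | 80.6% | 82.0% |
| 10% | 5.4% | 3.9% | 81.3% | 84.0% |

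**Simulation check.** There were 3,000 trials per scenario, with 256 women analysed, 15 centres × 2 × 2 strata, permuted blocks of 4 and SD 19.4. Repeat surgery was set at 20% and late entry at 10%. Apart from the 256 and the approximate number of centres, the settings are assumptions; the SD is the value implied above. Type I error is shown for the model with age, surgery and RT, then for the model that adds centre and the other two stratifiers. Monte Carlo error is about √(0.05 × 0.95/3000) = 0.004.

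| Centre ICC | Effect of each other stratifier | Listed covariates only | Stratifiers added |
|---|---|---|---|
| 0.01 | 0 points | 0.057 | 0.058 |
| 0.01 | 4 points | 0.051 | 0.052 |
| 0.05 | 4 points | 0.048 | 0.047 |
| 0.10 | 8 points | 0.035 | 0.045 |

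In the last scenario the smaller model reports a mean SE of 2.48, while its estimate actually varies with an SD of 2.32. A visible mismatch appears only there, and it is in the conservative direction.

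**The case against.** The strongest reply is that the effect is probably slight and that the analysis plan may already deal with it. Several parts of that reply stand.

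- A reader might infer that all three stratifiers are absent from the analysis. The text does not support that. RT and type of surgery may carry part of two of them, and centre may enter through the multilevel model.
- Timing is not ignored. A planned sensitivity analysis compares the interval between randomisation and surgery across groups. It does not put late entry into the primary model.
- A large R² is hard to justify. The only clustering figure given is an ICC of 0.01, and it is for therapists. With SD 19.4, one binary stratifier present in 20% of women (assumed) would need a difference of 19.4 × √(0.10/0.16) = 15.3 DASH points to explain 10% of the variance, over twice the 7-point target. Several factors could combine, and the different baseline state of late entrants could widen differences in change scores, but the documents measure neither.
- Balance may be incomplete. With 15 to 17 centres there are 60 to 68 cells for 350 women, about 5 to 6 per cell. The formula then overstates the error in the SE.
- A reader might also suppose that most women randomised before surgery have RT. The article gives no proportion.

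Deferral to the analysis plan does not dispose of the point. The article states a covariate list and a data-dependent rule for centre, and these do not match the randomisation it describes. How the two listed terms are coded can fairly be left to that plan.

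**Conclusion.** The point holds in a limited form. The listed covariates name none of the stratifiers, two of them are at best partly represented, and retention of centre depends on a check of the data. For an assumed residual R² of 1% to 10%, the SE is about 0.5% to 5.4% too large and the loss of power is about 0.3 to 2.7 percentage points. The lower end is the more plausible if the listed covariates already absorb much of the stratifiers' effect.

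It would be wrong to read this as a threat to validity. In the linear model, leaving out balanced factors does not bias the treatment difference, and the true type I error falls below 5% rather than rising above it. The stated sample size is unaffected. The case for change is that the gain costs nothing.

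**What to change.** In the primary adjusted model, include first/repeat surgery and late-entry status as fixed effects, coded as used at randomisation. Keep centre as a random or fixed intercept whatever the clustering check shows. Retain age, type of surgery and RT, and say how the last two relate to the stratifiers. Name this adjusted estimate as primary and the unadjusted one as supportive, so that the choice is settled before results are seen.

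The cost is a few lines in the protocol or the analysis plan. The variables were needed to randomise and so are already held. No further data or participants are required.

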#### Overview of exercise intervention

The intervention is predominantly delivered in physiotherapy outpatient departments. The first physiotherapy session is arranged 7–10 days after surgery, for assessment of shoulder ROM, postoperative pain, function, arm swelling, patients’ goals and assessment of confidence to carry out prescribed exercises. Participants are prescribed an individually tailored home exercise programme and provided with guidance on rehabilitation, management of postoperative complications and returning to general physical activity and/or work. The intervention targets three movement directions using a combination of active-assisted ROM, active ROM and stretches: shoulder flexion (forward), shoulder abduction (side) and abduction with external rotation (open chest). The second appointment is between 4–6 weeks postoperatively to review progress and prescribe shoulder strengthening exercises. The programme is progressed by increasing exercise repetitions, sets and resistance. The third appointment is recommended for between 12 and 16 weeks postoperatively, for further progression to facilitate return to work, sport and hobbies. For women with later entry on the basis of postoperative RT, these timings will be slightly delayed, but the prescribed exercise programme should commence at the earliest opportunity, thus within 6 weeks of surgery.

As per development work with patient representatives, and to reflect the pragmatic trial design, three additional physiotherapy consultations are available on request. The timing and delivery of additional appointments, either via telephone or face-to-face, are flexible to account for ongoing treatment, physiotherapist judgement and patient preference. Ideally, the intervention will be completed within the first 6 months following surgery, but women can contact their physiotherapist for up to 12 months after randomisation. Thus, any late treatment-related shoulder problems will be dealt with by the trial physiotherapist. Number and method of physiotherapy contacts will be closely monitored during the trial.

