## Outcomes

Figure 1 and table 3 present the study outcome measures and standardised assessment scales by assessment time point. Questionnaires are completed at baseline on recruitment, then at 6 weeks, 6 and 12 months after randomisation by post. The primary outcome is upper limb function at 12 months measured using the Disabilities of Arm, Shoulder and Hand (DASH) questionnaire.^14^ We considered other patient-reported outcome measures, including shoulder-specific scales, however selected the DASH because it captures symptoms and function of the upper limb rather than the shoulder joint per se. There is good evidence to suggest that women experience a variety of difficulties and restrictions after breast cancer treatment, affecting the hand, arm and shoulder. Functional impairment to the arm can affect performance of simple daily activities, including writing, opening or closing jars, lifting and/or holding shopping bags.

**Table 3 T3:** Outcome assessment

Outcome	Domain	Scale/measure	T_0_ baseline	t_1_ 6 weeks	t_2_ 6 months	t_3_ 12 months
Primary	Function	DASH				√
Secondary	Function	DASH subscales	√		√	√
	Acute and chronic pain Neuropathic pain	FACT-B4; NRS DN4	√ √	√ √	√ √	√ √
	Complications	SSI+self-report		√	√	√
	Lymphoedema	Self-report	√	√	√	√
	Health-related QoL	SF12/EQ-5D-5L	√		√	√
	Resource use	Self-report			√	√
	General activity and exercise	PASE items	√	√	√	√

DASH, Disabilities of Arm, Shoulder and Hand questionnaire; DN4, Doleur Neuropathique; EQ-5D-5L, Euroqol; FACT-B4, Functional Assessment of Cancer Therapy-Breast; NRS, numerical rating scale; PASE, Physical Activity Scale for the Elderly; QoL, quality of life; SF12, Short Form-12; SSI, surgical site infection; t, time point.

The DASH is a 30-item patient-reported outcome measure designed to capture difficulty in performing various upper arm activities.^14 15^ A single DASH score is generated, although psychometric assessment using discriminant content validation analysis has shown that the scale can be used to produce three health outcome subscores for impairment, activity limitation and participation restriction, as per the WHO International Classification of Functioning Disability and Health taxonomy.^16^

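### The timing sensitivity analysis is worded as a between-arm balance check, so no 6-week effect is re-estimated allowing for late entry or time since surgery

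*Protocol article*

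**What the plan says.** All from the protocol article:

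- **Outcomes.** Follow-up is timed from randomisation: "Questionnaires are completed at baseline on recruitment, then at 6 weeks, 6 and 12 months after randomisation by post". Table 3 lists pain, neuropathic pain, complications including surgical site infection, and lymphoedema at 6 weeks. DASH is not collected at that visit.
- **Allocation sequence generation and randomisation.** One stratification variable is "iii) whether informed of the need for RT within 6 weeks of surgery". It is explained by "whether participants are randomised preoperatively (up to the day of surgery) or within the first 6 weeks postoperatively".
- **Overview of exercise intervention.** The programme is timed from surgery: "The first physiotherapy session is arranged 7–10 days after surgery". For late entrants the timings shift somewhat later.
- **Data analysis.** Estimates will be "unadjusted and adjusted (for age, type of surgery and RT) estimates". Sensitivity analysis (b) is "assessment of differences between date of randomisation and date of surgery across groups, as surgical trials vary in relation to timing of follow-up". Further detail is left to a separate statistical analysis plan.

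**The concern.** The reason given for (b) is that follow-up timing varies. The method given does not address that reason. A sensitivity analysis normally re-estimates the effect under a changed condition. This one, read as written, sets the gap in one arm beside the gap in the other. Allocation is 1:1 and stratified on late entry, so the two are expected to agree however widely postoperative time varies within each arm.

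Nothing else named in the article covers the point. Late entry is a stratification factor but not a listed covariate. Radiotherapy is listed but is not the same thing: Table 2 also admits women whose radiotherapy was already planned before surgery, and they are not late entrants.

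At stake are the 6-week results. They pool women at quite different stages of wound recovery, with no stated analysis that separates them.

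**Working it through.** The plan gives no figure on this point to reproduce. The check has three parts.

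**1. Postoperative time at each visit.** Let g be weeks from randomisation to surgery for a woman randomised beforehand, and h (0 to 6) weeks from surgery to randomisation for a late entrant. The nominal 6-week visit falls at 6 − g or 6 + h weeks after surgery, and the 12-month visit at 52 − g or 52 + h. The article states no limit on g, so the non-zero values are assumptions.

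| Largest g (weeks) | 6-week visit, weeks after surgery | 12-month visit, weeks after surgery | Spread as share of 52 weeks |
|---|---|---|---|
| 0 | 6 to 12 | 52 to 58 | 6/52 = 12% |
| 2 (assumed) | 4 to 12 | 50 to 58 | 8/52 = 15% |
| 4 (assumed) | 2 to 12 | 48 to 58 | 10/52 = 19% |

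Even with no preoperative gap, postoperative time can double within the 6-week visit. At 12 months the spread is modest.

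**2. Size for 6-week pain.** Assumptions: g uniform on 0 to 4 weeks, h uniform on 0 to 6, late-entry share p of 5% to 20%, pain falling linearly by b = 0.2 to 0.5 points a week, and residual SD 2.3 (variance 5.29).

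- Preoperative entrants: mean 6 − 2 = 4 weeks, variance 16/12 = 1.333. Late entrants: mean 6 + 3 = 9 weeks, variance 36/12 = 3.
- Variance within strata = (1 − p) × 1.333 + p × 3. Variance between strata = p(1 − p) × (9 − 4)².
- p = 5%: 1.417 + 1.188 = 2.604, SD 1.61 weeks.
- p = 10%: 1.5 + 2.25 = 3.75, SD 1.94 weeks.
- p = 20%: 1.667 + 4 = 5.667, SD 2.38 weeks.
- Share of pain variance explained = b²V/(b²V + 5.29). Lowest: 0.04 × 2.604 = 0.104, and 0.104/5.394 = 1.9%. Highest: 0.25 × 5.667 = 1.417, and 1.417/6.707 = 21.1%.
- Using only the within-stratum variance: 0.057/5.347 = 1.1% to 0.417/5.707 = 7.3%.

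In terms of the model-based standard error:

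- Adding the late-entry stratum reduces it by 1 − √(5.347/5.394) = 0.4% to 1 − √(5.707/6.707) = 7.8%.
- Adding exact timing within stratum reduces it by a further 1 − √(5.29/5.347) = 0.5% to 1 − √(5.29/5.707) = 3.7%.

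These figures concern a pain score and do not carry over to the binary outcomes.

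**3. Effect on 12-month DASH.** The article gives no SD. Solving its 242 participants (121 per arm, 7 points, 80% power, two-sided 5% assumed) gives SD = 7/(1.960 + 0.842) × √(121/2) = 19.4. A simulation used the article's 256 analysed women, 1:1 allocation stratified by late entry, late-entry shares of 5% to 40%, the same g and h, and DASH slopes of 0 to 1 point a week.

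- The between-arm difference in mean gap averaged 0.00 to 0.02 weeks (SD 0.15 to 0.18), so check (b) would nearly always look balanced.
- The 7-point effect was recovered at 6.9 to 7.1. The standard error was 2.39 to 2.49 without a timing covariate and 2.38 to 2.49 with it.
- In a further run the effect was set at 7 for randomisation on the day of surgery, falling by 0.5 points for each week later, with 20% late entry. The mean position is 0.2 × 3 − 0.8 × 2 = −1.0 week, so the average effect is 7 + 0.5 = 7.5. The simulation gave 7.5 with or without a main-effect timing covariate. That is the correct average for that mix of women, but neither the balance check nor the covariate would show that the effect varied.

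**The case against.** The strongest answer is that the article defers detail to an analysis plan that is not shown, and its list of sensitivity analyses is not presented as complete. Item (b) is one condensed clause, and the plan may turn it into a re-analysis. This stands as a limit: a reader might infer that the trial will never re-estimate the effect, and the article does not show that. The point survives because the article states both a purpose and a method that do not match, and leaves a factor it randomises by out of the covariates it names.

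Other stronger readings also fail:

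- **That the timing spread biases the comparison or threatens the primary result.** Randomisation balances timing in expectation, and part 3 shows 12-month DASH practically unchanged.
- **That (b) is empty and should be replaced.** For women randomised before surgery, the surgery date follows an open-label allocation. A between-arm check on whether allocation shifted surgery dates has value.
- **That by the 6-week visit some women have had one session and others several.** The schedule supports about one or two for women randomised before surgery, and no session timetable is given for late entrants.
- **That a timing covariate would show whether the early effect depends on time since surgery.** A main effect cannot do this. It needs a restricted analysis or an interaction.

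It is also fair that the 21% needs the extreme inputs. A fall of 0.5 points a week from week 2 to week 12 is 5 points on a 0–10 scale.

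**Conclusion.** The point holds as a minor improvement. As worded, (b) is a descriptive balance check, and the article names no analysis of the 6-week outcomes that allows for late entry or time since surgery. The consequence is avoidable noise and blurred interpretation in secondary 6-week results.

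The 6-to-12-week range follows from the article alone. The variance and standard-error figures rest on assumed gaps, late-entry share, pain slope and SD, and their upper ends are best read as ceilings. Most of the removable noise at the upper end comes from late entry itself, which the trial already records.

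**What to change.** 1. Keep (b), described as a between-arm balance check.
2. Add the late-entry stratum as a covariate in the outcome models, chiefly the 6-week ones.
3. Add a sensitivity re-analysis of the 6-week outcomes restricted to women randomised before surgery.
4. Optionally, within that sensitivity analysis, add weeks from surgery to the scheduled assessment as a covariate, and a treatment-by-timing interaction labelled exploratory.

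The cost is a few sentences in the analysis plan and a little extra analysis. Both dates are already needed for (b), so no new data are required. The restricted analysis will be less precise. For women randomised before surgery, the timing covariate is fixed only after randomisation, so it belongs in a sensitivity analysis read alongside the balance check, not in the main model.
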